### Assessments

All participants will fill out questionnaires at 7 time points: at baseline, 3, 6, 9, 12, 18 and 24 months. The primary outcomes are symptoms of depression and anxiety as measured by the PHQ-9 and GAD-7 [31,32]. The PHQ-9 is a screening tool that has nine items that correspond to the nine DSM-IV criteria of depression [31]. With the PHQ-9 the patients are asked how often in the last two weeks they were bothered by nine problems such as " Little interest or pleasure in doing things". Each item can be scored from 0 ("not at all") to 3 ("nearly every day"). The total score on the PHQ-9 ranges from 0 to 27. This score indicates the severity of the depressive symptoms; the higher the score, the more severe [31]. A study with primary care patients with diabetes found an optimal cut off score for depression screening of 7 [33]. The cut-off point of 7 on the PHQ-9, was the most optimal cut off score to predict major depressive disorder measured by a diagnostic interview [33]. Therefore the cut-off of PHQ-9 ≥ 7 will be used in this study. The GAD-7 will be used to assess anxiety symptoms. This questionnaire has been developed to assess generalized anxiety disorder, but can also be used as a screener for several anxiety disorders [32]. A cut-off score of 8 has been found to be the most optimal cut-off score, when used as a screener for several anxiety disorders [32]. Therefore, patients with a score GAD-7 ≥ 8 are considered as having significant anxiety symptoms.

During the baseline interview the Mini International Neuropsychiatric Interview (MINI) is administered to assess major depression and general anxiety disorder. The MINI will not be used as a selection criterion.

Secondary outcomes are quality of life, health status, diabetes specific distress, self-management, medication adherence, and cost-effectiveness. Baseline and 12, 24 months HbA1c will be obtained from the patients' charts, to evaluate the effect on blood glucose. Furthermore, we will gather data regarding demographics (age, gender, marital status, and education), exercise (measured with SQUASH [34]), smoking and alcohol use, body mass index, psychiatric history, sleep impairment, and Type D (distressed) personality (DS-14 [35]). Type D is a personality type that is characterised by negative affectivity and social inhibition. Research on Type D personality has been mostly conducted in cardiac patients. In this population, it has been found that persons with Type D personality have a three-fold risk of adverse cardiac outcomes [36].

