In the present study, we therefore aim to test the effectiveness of a disease management intervention. It will be tested whether and to what extend the **Di**sease **Ma**nagement intervention for **Co**-morbid **De**pression and **A**nxiety in patients with **DM2**(DiMaCoDeA-DM2) can significantly reduce symptoms of depression and anxiety. Using a randomised controlled trial design, we will compare the new intervention to care as usual. Our primary objective is to investigate the effectiveness of the disease management approach on symptoms of depression and/or anxiety. Our secondary objectives are to investigate whether this approach results in improved quality of life, reduced diabetes-specific emotional distress, improved lifestyle and self care behaviours, and lower health care costs.

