### Power

Assuming an α of 0.05 and a 1-β (power) of 0.90, 64 participants are needed in each condition to be able to detect a moderate effect of 0.5 standard deviation on the PHQ-9 and GAD-7. We anticipate a drop out of 20% and therefore we will need to include 80 patients in both groups.

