### Statistical analyses

The data will be analysed using intention to treat approach. This means that participants are analysed in the group to which they are allocated, even though the participant did not start the intervention or did not complete the intervention. To test whether the intervention group differs from the control group in terms of demographical and clinical data, T-tests and Chi-square analyses will be used. To test the efficacy of the intervention in achieving favourable outcomes, ANCOVA's will be conducted. The analyses will be adjusted for the possible confounding variables age and sex.

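### Two primary scales measured at six follow-up visits, with neither a primary time point nor a rule on whether one or both must succeed

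*Protocol article*

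**What the plan says.** All references are to the protocol article.

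- **Assessments:** "The primary outcomes are symptoms of depression and anxiety as measured by the PHQ-9 and GAD-7". Questionnaires are completed at baseline and at 3, 6, 9, 12, 18 and 24 months, so there are six follow-up visits. None is marked as primary.
- **Background, objectives:** "Our primary objective is to investigate the effectiveness of the disease management approach on symptoms of depression and/or anxiety". Earlier in the same paragraph the aim is put as a significant reduction in symptoms of both conditions, joined by *and*. The abstract and the Discussion also use *and*.
- **Power:** "Assuming an α of 0.05 and a 1-β (power) of 0.90, 64 participants are needed in each condition", in order "to be able to detect a moderate effect of 0.5 standard deviation on the PHQ-9 and GAD-7". There is one alpha, with no division across scales or visits.
- **Statistical analyses:** "To test the efficacy of the intervention in achieving favourable outcomes", ANCOVAs (plural) are planned, adjusted for age and sex. The section gives no visit, no order of testing and no rule for combining the two scales.
- **Intervention and Blinding:** the programme runs for one year. Patients, therapists and researchers are not blinded.

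**The concern.** A primary claim needs an outcome, a time point and a rule for success. The article supplies two outcomes and leaves the other two elements open.

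The success rule determines which error is at risk. If benefit on either scale is enough, testing each at 0.05 pushes the family-wise error above 5%. If both scales must show benefit, the error is controlled but power falls below that for a single scale. The one alpha and one power in the Power section cannot be attached to a claim until the rule is known.

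The open time point matters more. Month 12 (end of the programme) and month 24 (end of follow-up) are both natural choices, and earlier visits could be defended too. Both scales are self-reported and the researchers know the allocation, so the visit presented as primary could be chosen after the results are seen.

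**Working it through.** **Inputs from the article.** Alpha 0.05 (sidedness not stated; two-sided taken here), effect 0.5 SD on each scale, 64 evaluable per arm, two primary scales, six follow-up visits, stated power 0.90.

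**Assumptions.** The article gives no correlations. I take the correlation between the two scales as 0.5-0.8 for the two-test results, and 0.6-0.7 for the twelve-test results together with a correlation between visits of 0.5-0.7. Test statistics are treated as normal.

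**1. The plan's own figure, one scale at one visit.** The expected z-statistic is 0.5 × √(64/2) = 2.83. Power is Φ(2.83 − 1.96) = 0.81 (0.80 by the t-test). The stated 0.90 is not reproduced without an unstated gain such as baseline adjustment. That is a separate issue; the point here is that the single-scale starting value is about 0.81.

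**2. Either scale, one fixed visit, each at 0.05.** If independent, the error is 1 − 0.95² = 9.75%. With correlated statistics:

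| Correlation between scales | Any false positive, two-sided | False benefit only (nominal 2.5%) |
|---|---|---|
| 0.5 | 9.1% | 4.5% |
| 0.6 | 8.8% | 4.4% |
| 0.7 | 8.4% | 4.2% |
| 0.8 | 7.8% | 3.9% |

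**3. Worst case: any win among 2 × 6 = 12 tests, each at 0.05.** If independent, the error is 1 − 0.95¹² = 46%. Simulation of 12 correlated statistics gives:

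| Between scales | Between visits | Any false positive, two-sided | False benefit only |
|---|---|---|---|
| 0.6 | 0.5 | 34% | 17% |
| 0.6 | 0.7 | 27% | 14% |
| 0.7 | 0.5 | 32% | 16% |
| 0.7 | 0.7 | 26% | 13% |

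**4. Both scales must succeed at one visit, each at 0.05.** No alpha split is needed. Joint power is the probability that both statistics exceed 1.96 when each has mean 2.83. It is 0.70 at correlation 0.5 and 0.74 at 0.8.

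**5. Either scale with family-wise control at one visit.** For a given scale tested at 0.025, the critical value is 2.24 and power is Φ(2.83 − 2.24) = 0.72 (0.71 by the t-test). Power to succeed on at least one scale, when both true effects are 0.5 SD, is 0.81-0.86 with Holm and 0.82-0.87 with Hochberg; the lower end is at correlation 0.8.

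**The case against.** A reader might infer that the plan is to run twelve ANCOVAs and claim success on any one of them, so that the false-positive rate as written is 26-34%. The documents do not support that. The objective describes what will be investigated; it is not a decision rule. Its *and/or* may simply echo the eligibility criterion, which admits patients with raised scores on either scale, and other sections say *and*. The plural ANCOVAs is explained by two primary and several secondary outcomes. Nothing says that each visit is tested separately.

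The two-sided figures also count false findings of harm. For the claim the trial wants to make, the rates are about half as large. With one visit fixed, even the two-sided rate is only 8-9%.

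Finally, this is a condensed article, and the method of multiplicity adjustment is commonly left to a statistical analysis plan. Its absence here is not counted as a fault.

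All of this limits the size of the point, but the point itself remains. The primary visit and the success rule belong to the definition of the primary endpoint. The article lists every visit and has separate sections on power and analysis, yet fixes neither, and its wording points to two different rules.

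**Conclusion.** The point holds in a limited form: the primary claim is not fully defined, because neither its visit nor its success rule is fixed. What follows depends on how the gap is filled.

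- Either scale at one pre-set visit: a modest inflation, to about 8-9% two-sided, or 4-4.5% for false benefit against 2.5%.
- Any scale at any visit: a large inflation, 26-34% two-sided or 13-17% for false benefit. This is an upper scenario that the text leaves open, not the stated plan.
- Both scales at one pre-set visit: no inflation, but joint power of about 0.70-0.74 against the stated 0.90. Part of that gap is already present for one scale (0.81).

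The facts are certain. The percentages rest on assumed correlations and should be read as ranges. The change should be made before any unblinded comparison.

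**What to change.** 1. Name one primary time point for both scales. Month 12 is an obvious candidate because it is the end of the one-year programme. Declare the other five visits secondary.
2. State the success rule: either benefit on at least one scale, with Holm or Hochberg at family-wise 0.05, or benefit on both scales, each tested at 0.05.
3. Use the same wording in the objective, the Power section and the Statistical analyses section, and restate the power for the chosen rule.

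**Cost.** The edit is to wording only, but the power consequence has to be disclosed. At 64 per arm and before any baseline-score adjustment (which the Statistical analyses section does not name), power is about 0.71 for a given scale tested at 0.025, about 0.81-0.87 for success on at least one scale, and about 0.70-0.74 for success on both. Keeping 0.90 for each scale at 0.025 would take 100 evaluable patients per arm, or 100/0.8 = 125 with the planned 20% dropout. If the baseline score were added to the model and correlated 0.5-0.6 with follow-up (an assumption), power for a given scale at 0.025 would be about 0.84-0.90 with 64 per arm.

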### Blinding

The nature of the study does not allow blinding of patients, therapists and researchers.

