### Randomisation

Patients will be randomised on patient level in equal ratio (1:1). Block randomisation will be used with block sizes of 2 and 4. These block sizes are chosen to enhance the chance that in each general practice patients will be in both study conditions. An independent researcher will generate a random sequence by http://randomization.com and will fill envelopes with the sheets describing the group allocation. These opaque envelopes will be sealed and sequentially numbered by the independent researcher. When a participant is enrolled in the study, the person who enrols the participant will open the envelope and disclose the group allocation. The allocation sequence will be concealed until a participant is irreversibly registered.

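### The blinding statement is too broad: the analyst can be masked, and perhaps the HbA1c extractor, although the gain is small

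*Protocol article*

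**What the plan says.** The Blinding section of the protocol article is a single sentence: "The nature of the study does not allow blinding of patients, therapists and researchers". It does not divide researchers into roles, and no other section says who analyses the data or who extracts HbA1c.

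Four other statements bear on it:

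- **Primary outcomes (Assessments):** "The primary outcomes are symptoms of depression and anxiety as measured by the PHQ-9 and GAD-7". The participants complete both scales themselves: "All participants will fill out questionnaires at 7 time points: at baseline, 3, 6, 9, 12, 18 and 24 months".
- **HbA1c (Assessments):** "Baseline and 12, 24 months HbA1c will be obtained from the patients' charts, to evaluate the effect on blood glucose".
- **Analysis (Statistical analyses):** "To test the efficacy of the intervention in achieving favourable outcomes, ANCOVA's will be conducted", with adjustment for age and sex.
- **Allocation (Randomisation):** "An independent researcher will generate a random sequence" and prepares the sealed envelopes. At enrolment, "the person who enrols the participant will open the envelope and disclose the group allocation".

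**The concern.** The sentence does more than leave masking undescribed. It says that blinding of researchers, as a class, is ruled out by the kind of study this is. For a behavioural programme that reason covers those who receive it, deliver it, or must know the arm to do their job. It does not cover a person whose task can be done on a file in which the arms carry neutral codes.

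Two tasks are in question. The first is the analysis. The article names the method and two covariates but does not say which scale or visit is decisive, so choices may remain when the data are seen, and an analyst who knows the arms can be influenced by which arm a choice favours. The second is taking HbA1c from routine charts. If more than one value lies near 12 or 24 months, someone must pick one. Better glycaemic control is one of the hypotheses in the Discussion, so that choice is not neutral for a person who knows the arm.

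**Working it through.** The article gives no figure on blinding, so there is none to reproduce. The check takes each role and asks whether the intervention itself prevents masking.

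| Role | What the article says | Does the intervention prevent masking? |
|---|---|---|
| Patients | Receive lessons, a coached self-help course and possibly medication (Stepped care), or usual care (Control group) | Yes |
| Therapists | Psychologists give the lessons and coaching (Stepped care) | Yes |
| Enrolling staff | Open the envelope (Randomisation) | Yes, under the stated procedure |
| Staff who act on scores | Intervention arm: PHQ-9 ≥ 7 or GAD-7 ≥ 8 leads to an offer of treatment (Monitoring). Control arm: consecutive scores ≥ 15 on either scale lead to notice to the GP (Control group) | Yes, because the action depends on the arm |
| Analyst | Not named; runs ANCOVAs (Statistical analyses) | No, coded arms are sufficient |
| HbA1c extractor | Not named; values come from charts (Assessments) | Not in principle, but charts may reveal the arm |

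**Outcome raters.** PHQ-9 and GAD-7 are self-completed. The only interviewer-administered instrument named, the MINI, belongs to the baseline interview, and Study setting and sample recruitment places randomisation after that interview. No interviewer-rated outcome after randomisation is named, so no such rater needs masking.

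**Choices exposed.** Inputs from Assessments: 2 primary scales; 7 time points including baseline.

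- Follow-up visits: 7 − 1 = 6 (3, 6, 9, 12, 18 and 24 months).
- Possible primary contrasts: 2 × 6 = 12.
- HbA1c follow-up times: 2 (12 and 24 months).

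These counts show how many places a choice could be made on the published text. They do not measure bias. Coding the arms leaves all 12 contrasts in place. It only prevents the choice among them from being steered by which arm benefits.

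**HbA1c selection.** Study setting and sample recruitment has patients seen by the practice nurse every three months. Several candidate values around a target date are therefore plausible, but this is an inference: the article states neither how often HbA1c is measured nor an extraction window.

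**The case against.** The strongest reply has four parts.

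1. **The roles are inferred.** The article never says that the analyst or the extractor sees the allocation, and masking details are often left to a full protocol or SAP, which is not shown. This stands in part: the article does not establish that either person will be unblinded. But it does not leave the matter open either. It declares researchers unblindable without exception, and a SAP that masked the analyst would contradict it.

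2. **Some researchers do need the arm.** A reader might infer that every data task, questionnaire entry included, could be masked. The documents do not support that. The Monitoring and Control group sections attach different actions to the scores in each arm, so whoever applies those rules must know the arm. Masked entry would need a separate unmasked person. No such demand is made here.

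3. **The 12 contrasts are a matter of pre-specification.** This is right. Coded arms do not replace naming the decisive scale and visit. Masking is a supplementary safeguard.

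4. **HbA1c leaves little room for judgement.** It is a recorded number and not a primary outcome. Coaching takes place in the practice and the GP offers medication, so the chart itself may disclose the arm. This stands, and it is why extractor masking is proposed only where feasible. A reader might also take HbA1c to be the only outcome that patients do not report. The article does not support this, since it gives no data source for cost-effectiveness or medication adherence.

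A reader might go further and infer that the plan knowingly accepts bias that it could remove. That is too strong. The main threat is self-report by patients who know their arm, on both primary outcomes, and neither measure touches it.

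**Conclusion.** The concern holds in limited form. The stated reason is too broad: it justifies not blinding patients, therapists, and staff who enrol patients or act on scores, but not the analyst, and not necessarily the HbA1c extractor. The firm part is the analyst. The HbA1c part is weaker, because charts can reveal the arm and only the selection of a value is exposed.

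The consequence is a small, avoidable risk of bias, which cannot be quantified from the article. This conclusion assumes that researchers in the Blinding section includes whoever runs the analyses, which is the plain reading of an unrestricted word, and that some analysis choices remain open when data are seen. A SAP that fixes the decisive scale, visit and model would reduce what analyst masking adds. For HbA1c it also assumes that some patients have more than one eligible value. The larger risk from unblinded self-report remains whatever is done here.

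**What to change.** Replace the sentence in the Blinding section with text to this effect:

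> Patients, therapists and the staff who enrol patients or act on their scores cannot be blinded. The analyst works with coded arms until the analysis code and primary results are final; the code is held by someone not involved in the analysis (for example the independent researcher who generated the sequence). HbA1c values are extracted without access to the allocation list where feasible.

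The independent researcher is only an example: the Randomisation section gives that person the sequence and the envelopes, so holding the code would be an added task to agree.

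The cost is a recoding step and some data-management time to keep allocation out of the analysis file and, where possible, out of the extraction file. Treatment, visits and sample size do not change. The limitation to state openly is that masking of the HbA1c extractor may be incomplete.

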### Statistical analyses

The data will be analysed using intention to treat approach. This means that participants are analysed in the group to which they are allocated, even though the participant did not start the intervention or did not complete the intervention. To test whether the intervention group differs from the control group in terms of demographical and clinical data, T-tests and Chi-square analyses will be used. To test the efficacy of the intervention in achieving favourable outcomes, ANCOVA's will be conducted. The analyses will be adjusted for the possible confounding variables age and sex.

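### The ANCOVA's named covariates are age and sex; each primary scale's own baseline score is not named, so the analysis as written gives up precision

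*Protocol article*

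**What the plan says.** The efficacy method is given in one sentence of the Statistical analyses section: "To test the efficacy of the intervention in achieving favourable outcomes, ANCOVA's will be conducted". The next sentence names the adjustment variables: "The analyses will be adjusted for the possible confounding variables age and sex". The dependent variable is not described further, so the text does not say whether it is a follow-up score or a change from baseline.

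The Assessments section says: "The primary outcomes are symptoms of depression and anxiety as measured by the PHQ-9 and GAD-7". It also says: "All participants will fill out questionnaires at 7 time points: at baseline, 3, 6, 9, 12, 18 and 24 months". Under Study setting and sample recruitment, the baseline questionnaires are completed at an interview that comes before allocation. The baseline value of each primary outcome is therefore planned for every participant and cannot be affected by treatment.

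The Randomisation section describes 1:1 allocation in blocks of 2 and 4 and mentions no stratification by severity. The Power section plans for 64 analysed per arm and an effect of 0.5 SD, without mentioning a baseline correlation or a variance reduced by adjustment.

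**The concern.** In a randomised trial a covariate is worth including for its prognostic strength. Confounding, the reason the article gives for age and sex, is dealt with by the randomisation itself, as its Discussion acknowledges. On prognostic grounds the first candidate is the earlier value of the same scale, and that is the variable not named.

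Two things are at stake. The first is precision: residual variance that the baseline score could remove stays in the standard error of the treatment effect. The second is conditional accuracy: if one arm happens to start with more severe symptoms, part of that difference carries through to follow-up and is not removed. Randomisation is not stratified by severity, so nothing else in the article limits such an imbalance.

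**Working it through.** **Inputs from the article.** 64 analysed per arm, alpha 0.05 and an effect of 0.5 SD (Power); two equal arms (Randomisation). Sidedness is not stated, and two-sided is taken as the main case.

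**Assumed.** The correlation r between baseline and follow-up score, beyond age and sex. The article gives none, so a range of 0.3 to 0.7 is shown. The row r = 0 treats age and sex as explaining nothing. The 0.5 SD is taken in units of the unadjusted follow-up SD.

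**Step 1: the plan's own figure.** The Power section states: "Assuming an α of 0.05 and a 1-β (power) of 0.90, 64 participants are needed in each condition". For a two-sided comparison of means, n per arm = 2(z₀.₉₇₅ + z₀.₉₀)² / d² = 2(1.960 + 1.282)² / 0.25 = 84.1, so 85 (86 by the t test). The stated 64 is not reproduced. It is the t-test figure for 80% power: 2(1.960 + 0.842)² / 0.25 = 62.8, so 63 by the normal formula and 64 by the t test. A one-sided 5% test would need 69. The dropout step is right: 64 / 0.80 = 80. This discrepancy is a separate matter and is used here only to set the unadjusted starting point.

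**Step 2: effect of baseline adjustment.** Adjusting for the baseline score multiplies the residual variance by 1 − r², so the effect in residual SD units is 0.5 / √(1 − r²). Power comes from the noncentral t distribution with noncentrality [0.5 / √(1 − r²)] × √(64/2). At r = 0 this is 0.5 × 5.657 = 2.83. The degrees of freedom are kept at 126, since the few used by covariates make no practical difference.

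| r (assumed) | Residual variance, 1 − r² | Effect in residual SDs | Power, 64 per arm | n per arm for 90% (normal formula) |
|---|---|---|---|---|
| 0 | 1.00 | 0.500 | 0.801 | 85 |
| 0.3 | 0.91 | 0.524 | 0.837 | 77 |
| 0.4 | 0.84 | 0.546 | 0.865 | 71 |
| 0.5 | 0.75 | 0.577 | 0.900 | 64 |
| 0.6 | 0.64 | 0.625 | 0.939 | 54 |
| 0.7 | 0.51 | 0.700 | 0.976 | 43 |

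**Step 3: chance imbalance.** In SD units the difference in baseline means between arms has standard error √(2/64) = 0.177, so its 95% range is ±1.96 × 0.177 = ±0.35. If unadjusted, an imbalance at that limit moves the follow-up difference by about r × 0.346: 0.10 SD at r = 0.3, 0.17 SD at r = 0.5 and 0.24 SD at r = 0.7. The target effect is 0.5 SD. This describes an unlucky allocation; over repeated randomisations the shift averages zero.

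**The case against.** The strongest reply is that the text does not exclude baseline adjustment. Where an outcome is measured before and after treatment, ANCOVA is often used to mean a model that conditions on the baseline value, and age and sex may have been listed as extras. The sentence does not say that they are the only covariates. This stands as a statement about possible intent. However, a model with age and sex alone also satisfies the word ANCOVA, and the one sentence that lists adjustment variables leaves baseline out.

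Nor is the dependent variable stated; a change score would also use starting severity. That is true, but a change score is not equivalent. With equal variances at both times, its variance relative to the follow-up score is 2(1 − r), against 1 − r² for baseline adjustment: 1.40 against 0.91 at r = 0.3, and 1.00 against 0.75 at r = 0.5.

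A condensed article may leave detail to a statistical analysis plan. That would answer silence on covariates. Here a set is named, so adding baseline later would change or clarify a published choice.

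The size of the gain is uncertain. Long follow-up (to 24 months) and entry cut-offs could both lower r, and at 0.3 power rises only from 0.80 to 0.84. This stands in full. The range restriction is partial, because entry needs an elevated score on only one of the two scales.

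A reader might infer three stronger things that the documents do not support:

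- **That the effect estimate is biased or the primary test invalid.** Under 1:1 randomisation it is neither, and the unadjusted standard error already allows for chance imbalance on average.
- **That omitting baseline is what causes the shortfall against 90% power.** The Power section makes no use of covariate adjustment; its figure fails on its own inputs.
- **That the baseline t-tests and chi-square tests will drive covariate selection and should go.** The article names age and sex in advance and does not link those tests to the choice.

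**Conclusion.** The point holds as a loss of efficiency in a stated choice, or at the least as an ambiguity to be removed. As written, the ANCOVA's named covariates omit each primary outcome's own baseline score, which is planned for every participant before allocation. Validity is not in question. At 64 analysed per arm, 0.5 SD and two-sided 5%, adjustment would raise power from about 0.80 to about 0.84, 0.90 or 0.94 for r = 0.3, 0.5 or 0.6, and it would correct for chance imbalance in severity. The direction of the gain holds across the whole range shown; its size rests on the assumed r. That the baseline score is the strongest available predictor is a general expectation, not a figure from the article. The change should be made, but the trial's primary conclusion would not be unsound without it.

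**What to change.** Add to the Statistical analyses section that each PHQ-9 and GAD-7 ANCOVA includes that scale's own baseline score, from the pre-randomisation interview, as a continuous covariate alongside age and sex. State the same rule for secondary outcomes and HbA1c wherever a baseline value is collected. If baseline adjustment was already intended by the word ANCOVA, say so explicitly. Settle the wording before outcome data are examined by arm, so that the covariate set is not a later choice.

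The cost is one sentence and one degree of freedom per model. No further data or patients are needed. The baseline comparison tests can stay as they are for this purpose, and the sample-size figure needs its own correction whatever is decided here.
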